### Allocation to study arms

The recruited township or community health centers will be randomly allocated to TMP and UC arms at the same time after the completion of baseline data collection. The allocation process will be performed by an external statistician via 4 steps. Step 1, the project facilitator sends, via email, the allocation requirements alongside the name-list of the 6 selected counties and the 4 health centers recruited under each of the counties to the external statistician. Step 2, the statistician performs the random assignment of the health centers into equal arms of TMP and UC using the “random sample of cases” function in IBM SPSS on a county-by-county base so that the 4 health centers recruited from each of the site counties is randomly assigned as 2 to the TMP arm and the other 2 to the UC arm. Step 3, the statistician emails back the resultant allocation to the project facilitator. Step 4, the facilitator communicates the allocation to the participating physicians and arranges the planned training for those in the TMP arm.

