#### Message sending

The whole process of the message selection, modification (substitution of embedded variables), and sending will be by a user-friendly mini computer program. The program automatically extracts data about the patient’s name, symptoms, and diagnosis from the electronic medical record system routinely in use at all the participating clinics and then translates all the substitution variables into personalized texts. So, implementation of the intervention incurs little additional workload for the participating doctors. What the doctors need to do is limited to obtaining informed consent and cell phone numbers from the patients and adding them into the list eligible to receive the TMP; Fig. 2 illustrates how the mini program works. The upper part of the figure provides a name list of all the messages to be sent out to patients. The middle part shows an example message template and the doctor is allowed to modify the template for his/her own patients, while the lower part presents all the substitution variables capable of being automatically translated.

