### Trial evaluation

#### Outcome measures

The primary outcome is the number of days of antibiotics use, including antibiotics obtained before and after the initial consultation. The secondary outcomes include (1). illness duration and severity, (2) patients’ attitude and understanding of intervention messages, (3) patients’ quality of life, (4) re-visits and antibiotic usage, (5) patients’ knowledge and attitude toward antibiotics, and (6) recurrence of RTIs and related health service and antibiotics use. Definition and calculation of these measures are summarized in Table 2.

**Table 2 Tab2:** Primary and secondary measures for trial evaluation

Measure	Definition/calculation

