#### Sample size

The sample size of patients to be recruited for the trial evaluation is calculated on the basis of the primary outcome measure above. Our previous study [18] estimated that the number of days of antibiotic use by symptomatic RTI patients was 4.35 $$\pm$$ 2.06 for rural township health centers in Anhui province. There is no internationally agreed minimally important difference in the days of patients using antibiotic. However, we anticipate that a reduction of at least 15% in the days of antibiotic use would represent a meaningful change at the population level. So, we assume the following: (1) the intervention group is 20% lower than the control group, i.e., a reduction of about 0.87 days; (2) standard deviation of the days of antibiotics use is 2.06 days; and (3) the alpha value is 0.05. Given these, to detect a possible absolute difference of 0.87 days in the rates with 90% power, we will need 118 RTI patients in each arm. Based on our previous study results the estimated design effect value would be 2.45. By allowing for a 20% attrition rate and for a 20% loss to follow-up rate, therefore we would aim to recruit at least 2.45×118×2×1.2×1.2=833 patients into the study and this translates into about 35(833/24=35) patients per township/community health center.

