#### Data analysis

The data collected will be used to compare the differences between the control and intervention groups as a whole and between subgroups in the intervention arm in terms of days of antibiotic use per episode of RTIs; times of re-visits to clinics and antibiotics re-prescription for the same RTI; quality of life; times of re-occurrence of RTIs and related health service seeking and antibiotics consumption for re-occurred infections; and scores of patients’ knowledge about and attitude toward antibiotics.

Estimation of statistical significance and confidence intervals will assume a type I error established in alpha=0.05, using the IBM SPSS V25 statistics package. Missing data will be treated as missing at random and imputed using a chained-equations multiple imputation model. Initial data analysis will consist of descriptive summaries intended to examine the patterns of the various measurements and check for normality of the continuous variables. And necessary transformations will be explored and selected, if necessary, to induce approximate normality. Regarding the numerical variables between two groups, *t*-test of independent samples for mean comparisons will be carried out. The chi-square test will be conducted for categorical variables (non-continuous). Lastly, no interim analysis is planned.

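### The primary t-test uses neither the county strata of the allocation nor any baseline information, which gives up precision when about 60% of the variance of an arm mean lies between centres

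*Protocol article*

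**What the plan says.** The Data analysis section fixes the method for numerical variables: "test of independent samples for mean comparisons will be carried out". It mentions no covariate, centre effect or county term. The primary outcome to which this applies is defined under Outcome measures: "The primary outcome is the number of days of antibiotics use, including antibiotics obtained before and after the initial consultation".

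Other sections show what the comparison leaves unused:

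- **Allocation to study arms.** Each of 6 counties contributes 4 centres, 2 to each arm, so 12 v 12 in all. The centres are "randomly allocated to TMP and UC arms at the same time after the completion of baseline data collection". What that baseline consists of at centre level is not defined. The only baseline described under Data collection is each recruited patient's interview directly after the consultation.
- **Sample size.** "Based on our previous study results the estimated design effect value would be 2.45". No intracluster correlation (ICC) is given. The target is "the intervention group is 20% lower than the control group, i.e., a reduction of about 0.87 days".
- **Message sending.** The mini-program takes patient name, symptoms and diagnosis "from the electronic medical record system routinely in use at all the participating clinics". Prescriptions are not mentioned among the extracted items.

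**The concern.** With 24 centres and a design effect of 2.45, much of the random error in the primary result comes from how antibiotic-heavy each centre already was. Recruiting more patients per centre reduces that component very little. More centres, the allocation strata, or information about the centres from before allocation would reduce it.

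The stated test uses none of these. A cluster-adjusted standard error would report the centre noise honestly but would not reduce it. Leaving county out of the model also forgoes the precision that stratified allocation has already bought, because between-county variation then stays in the estimated error. At stake are the width of the confidence interval and some power. A chance split of heavy and light prescribers within counties would also remain in the estimate uncorrected.

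**Working it through.** **1. The plan's own figures.** Inputs from Sample size: difference 0.87 days, SD 2.06, "the alpha value is 0.05" (two-sided reproduces the result), power 90%.

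- n per arm = 2 × [2.06 × (1.960 + 1.282) / 0.87]² = 117.8, so 118 as stated.
- Analysable total = 2.45 × 118 × 2 = 578. Multiplied by 1.2 × 1.2 this is 832.6, so 833 as stated.

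**2. Implied ICC.** ICC = (2.45 − 1)/(m − 1). The protocol does not say to which cluster size the 2.45 belongs, so two values are shown.

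- m = 578/24 = 24.1 analysed per centre: 1.45/23.1 = 0.063.
- m = 35 recruited per centre: 1.45/34 = 0.043.

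**3. Between-centre share of the variance of an arm mean.** Share = m × ICC / 2.45.

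- m = 24.1: 0.617.
- m = 35: 0.609.
- Over m = 20 to 100 it stays between 62% and 60%, so the figure hardly depends on m.

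**4. Chance arm difference from centres alone.** Let f be the fraction of centre variance that lies between counties (not in the documents; assumed). Allocation of 2 v 2 within county removes that fraction from the arm difference, whether or not county is modelled. The SD is 2.06 × √[ICC × (1 − f) × 2/12].

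- f = 0, m = 24.1: SD 0.211, 95% range ±0.41 days (47% of 0.87).
- f = 0.5, m = 24.1: SD 0.149, ±0.29 days (34% of 0.87).
- m = 35: ±0.34 days (f = 0) and ±0.24 days (f = 0.5).

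The centre share of the variance of the *difference* at m = 24.1 is 62% for f = 0 and 45% for f = 0.5.

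**5. Effect of a centre-level covariate.** Let r be its within-county correlation with the centre's true mean outcome (assumed). With B = 0.063 × (1 − f) and W = (1 − 0.063)/24.1 = 0.039:

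SE = 2.06 × √{[B(1 − r²) + W] × 2/12}

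Power comes from the non-central t distribution at 0.87 days. Degrees of freedom with county in the model are 24 − 2 − 5 = 17, and 16 with the covariate.

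| | No covariate | r = 0.3 | r = 0.5 | r = 0.7 |
|---|---|---|---|---|
| SE, f = 0 | 0.268 | 0.261 | 0.247 | 0.224 |
| Power, f = 0 | 86.4% | 87.9% | 91.1% | 95.4% |
| SE, f = 0.5 | 0.223 | 0.219 | 0.210 | 0.197 |
| Power, f = 0.5 | 95.7% | 96.2% | 97.3% | 98.5% |

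If f = 0, the five degrees of freedom spent on county cost about one point: power is 87.3% on 22 degrees of freedom without it. If f = 0.5, the true SE is 0.223, while a cluster-adjusted analysis without county would report something close to 0.268.

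**The case against.** **Covariates belong in an analysis plan that is not shown.** This is partly right, and silence on covariates would be no finding. But the section does not leave the method open. It names an unadjusted two-sample test for a trial randomised by centre within county, so an analysis plan would have to replace that choice.

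**The centre noise is already paid for.** This stands. The factor 2.45 in the sample size covers between-centre variation, and chance differences between randomised centres are random error. A reader might infer that heavy-prescribing centres falling in one arm would bias the result. The documents do not support that. The loss is one of precision.

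**The 60% does not describe the arm difference.** This also stands. A reader might carry the share, or the ±0.41 days, straight over to the treatment effect. Both are upper limits, because allocation within county balances the between-county part.

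**The gain may be small.** This is fair.

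- Neither r nor f is in the documents, and it is not confirmed that the record holds prescriptions.
- The proxy may be weak. The outcome counts days, including antibiotics obtained before the consultation. The Background says pharmacies supply antibiotics without prescription and puts use in RTI patients above 80%, so the proportion prescribed may vary little between centres.

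**A saving in patients.** It is tempting to read the fall in design effect from 2.45 to 1.71 (r = 0.7, f = 0) as worth 2.45/1.71, or 43% more patients. That holds only if they come from additional centres. In the same 24 centres, 43% more patients (about 34.5 per centre) gives 24.1 × (0.063 + 0.937/34.5) = 2.17, not 1.71.

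**Conclusion.** The point holds as a matter of precision. The stated primary comparison ignores the county strata and all baseline information, in a design whose own design effect puts about 60% of the variance of an arm mean between centres.

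The size depends on two unknowns. With no centre variance between counties, chance centre differences span ±0.41 days, and a useful centre covariate takes power from about 86% to between 88% and 95%. With half of it between counties, the span is ±0.29 days, power with county modelled is already about 96%, and the covariate adds about 0.5 to 3 points. All these figures assume 578 analysable patients, 24 equal centres and a design effect of 2.45 at that size.

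Neglect of clustering in the standard error is a separate fault of the same test. It does affect validity: true type I error is about 2 × [1 − Φ(1.96/√2.45)] = 21% if f = 0, and about 13% if f = 0.5. A cluster-adjusted model cures that, but does not by itself recover the precision discussed here.

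**What to change.** - Make the primary analysis of antibiotic days a cluster-adjusted model with county as a fixed effect and patient age, already collected at baseline, as a prespecified covariate.
- Confirm whether the electronic record holds prescriptions. If it does, extract for each centre the proportion of adult RTI visits with an antibiotic over a fixed period before allocation. Add it as one centre-level covariate, with its definition fixed before unblinding.
- Do not use the baseline severity rating or the doctor's diagnosis as primary covariates. The interview follows the consultation and, by the Blinding section, doctors and interviewers know the arm, so both could be influenced by allocation. They can serve in sensitivity analyses.
- Report the cluster-level result without baseline covariates alongside.

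The cost is analysis wording, five centre-level degrees of freedom for county (22 to 17), one more for the centre covariate (17 to 16), and one retrospective extract for 24 centres. No change to recruitment or to the patient interviews is needed.

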### Trial design

The study adopts a cluster randomized controlled trial (RCT) design, involving two arms of equal townships or community health centers, i.e., the TMP arm or the UC arm.

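### The between-arm tests named for this cluster trial treat patients as independent, against the plan's own design effect of 2.45. For the primary outcome the nominal 5% test could have a true error of up to about 21% at that design effect

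*Protocol article*

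**What the plan says.** Trial design: "The study adopts a cluster randomized controlled trial (RCT) design, involving two arms of equal townships or community health centers". The health centre is the unit of randomisation.

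Allocation to study arms: randomisation is done separately in each county, with this result: "the 4 health centers recruited from each of the site counties is randomly assigned as 2 to the TMP arm and the other 2 to" usual care. With six counties, that is 24 centres, 12 per arm.

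Sample size: "Based on our previous study results the estimated design effect value would be 2.45". The patient number is multiplied by this factor.

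Data analysis: inference "will assume a type I error established in alpha=0.05, using the IBM SPSS V25 statistics package". Numerical variables are compared by a t-test "of independent samples for mean comparisons will be carried out. The chi-square test will be conducted for categorical variables (non-continuous"). The same paragraph says that "necessary transformations will be explored and selected, if necessary, to induce approximate normality". The article mentions no mixed model, GEE, cluster-robust variance, centre-level analysis or county term.

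**The concern.** The sample size section and the analysis section cannot both stand. The first accepts that patients of the same centre resemble one another enough to require 2.45 times as many of them. The second names tests whose standard errors are right only if there is no such resemblance. This is a stated choice, not a detail left to an SAP: an SAP that followed the article would be invalid, and one that corrected it would contradict the article.

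The primary p-value and confidence interval are at stake. If the standard error is too small, a chance difference between centres is too readily declared an effect of the messages.

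A smaller point belongs to the same test. The planned effect is 0.87 days. If a transformation is selected from the data, the primary estimate may no longer be a difference in days.

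**Working it through.** **Inputs.** From Sample size: mean 4.35 days, SD 2.06, difference 0.87, power 90%, alpha 0.05, design effect (DE) 2.45, two inflation factors of 1.2, 35 patients per centre. From Allocation to study arms: 6 counties × 4 centres. Sidedness is not stated; two-sided reproduces the plan's figure (one-sided would give 97 per arm).

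**1. The plan's own figures.** n per arm = 2 × [2.06 × (1.960 + 1.282) / 0.87]² = 117.8, so 118. Total = 2.45 × 118 × 2 × 1.2 × 1.2 = 832.6, so 833; 833/24 = 34.7, so 35 per centre. All reproduce.

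**2. Unadjusted test at DE 2.45.** The naive standard error is too small by √2.45 = 1.565. True two-sided type I error = 2 × [1 − Φ(1.96/1.565)] = 2 × [1 − Φ(1.252)] = 21.1%. A nominal 95% interval covers about 79%.

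**3. Fewer patients analysed.** Assume that 2.45 refers to 35 per centre. Then ICC = 1.45/34 = 0.0426 and DE = 1 + (m − 1) × 0.0426.
- m = 35/1.44 = 24.3: DE 1.99, error 16.5%.
- m = 35 × 0.8 × 0.8 = 22.4: DE 1.91, error 15.6%.

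**4. Part of the clustering between counties.** Let f be the county share of the ICC (an assumption; the article gives none). Each county contributes two centres to each arm, so its effect cancels from the difference. The effective DE is 1 + (m − 1) × ICC − m × ICC × f.

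| f | m = 35 | m = 22.4 |
|---|---|---|
| 0 | DE 2.45, 21.1% | DE 1.91, 15.6% |
| 0.3 | DE 2.00, 16.6% | DE 1.63, 12.4% |
| 0.5 | DE 1.70, 13.3% | DE 1.44, 10.2% |
| 1 | DE 0.96, 4.5% | DE 0.96, 4.5% |

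**5. Simulation** of the 6 × 4 stratified design (40,000 replicates per scenario). With no county share, the unadjusted t-test rejected in 21.1% (m = 35) and 16.3% (m = 24). At a 50% share it rejected in 13.4% and 10.8%. A county-adjusted test of centre means on 24 − 6 − 1 = 17 df held 4.9 to 5.2% in every scenario.

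**6. Other readings of 2.45.** The cluster size behind it is not stated. If it was 30, ICC = 1.45/29 = 0.05 and the error is 17.3% (m = 22.4) to 23.3% (m = 35). If it was 24.1, ICC = 1.45/23.1 = 0.063 and the range is 20.0 to 26.8%. Both assume no county share.

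**7. Where the conclusion would change.** With 833/2 = 416.5 per arm, the naive SE is 2.06 × √(2/416.5) = 0.143, so differences above 1.96 × 0.143 = 0.28 days are called significant. The valid threshold at DE 2.45 is 2.11 × 0.143 × 1.565 = 0.47 days. With 266 per arm and DE 1.91, the thresholds are 0.35 and 0.52 days.

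**The case against.** The article does not state the unit of analysis, so the t-test could in principle be run on centre means. That is a strained reading. A chi-square test on categorical variables needs patient counts, and the comparison is described per RTI episode. Even centre means would be tested without the county term.

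Four stronger readings are tempting, and the documents do not support them.

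- **Ignoring county inflates the error.** It does not. Allocation is balanced within county, so a between-county share makes the unadjusted test less liberal (step 4). Only the omission of health centre causes the inflation. County belongs in the model because randomisation was stratified by it.
- **The range of 16 to 21% is a fact about this trial.** It is conditional. The article gives neither the cluster size nor the level of clustering behind 2.45. Across the readings above, the error runs from about 5% (all clustering between counties) to 27%. Nothing in the article suggests the first extreme.
- **Every secondary comparison is wrong by the same amount, or no significant result could be trusted.** The 2.45 was applied to days of antibiotic use only, and no design effect is given for another outcome. For the primary outcome, the verdict changes only for differences between about 0.28 and 0.47 days, or 0.35 and 0.52 with fewer patients. Those lie below the 15% reduction that the plan calls meaningful (0.15 × 4.35 = 0.65 days) and below the planned 0.87. An effect of the planned size would survive correction, but its p-value and interval would still be wrong.
- **The imputation also ignores clustering.** The article names chained equations without listing the variables. That content is commonly left to an SAP, so its absence is no finding.

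On the transformation, the Blinding section keeps the analysing statisticians unaware of allocation until the analysis is complete. This guards against choosing a scale by its result. The change in what is estimated remains.

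None of this removes the mismatch between the named tests and the design.

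**Conclusion.** The analysis is wrong as written and must be changed. For the primary outcome, the nominal two-sided 5% test has a true type I error of about 21% at the plan's own design effect, or about 16% at 22 to 24 analysed patients per centre. This rests on two assumptions: that 2.45 refers to 35 patients per centre, and that the clustering lies between centres within county. A between-county share of 30 to 50% lowers the error to about 10 to 17%. For secondary outcomes the tests have the same fault, but its size cannot be derived from the document.

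**What to change.** For the primary outcome, replace the t-test with a linear mixed model on untransformed days: fixed effects for arm and county, a random effect for health centre, and a small-sample correction of the degrees of freedom (SPSS MIXED with Satterthwaite). A county-adjusted comparison of the 24 centre means on 17 df is an acceptable alternative. For the other between-arm comparisons, replace the t and chi-square tests with linear or generalised linear mixed models with a random centre effect, as the outcome type requires. State that the primary estimate stays on the scale of days, so that it answers the 0.87-day question, and withdraw the data-selected transformation for it.

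No new data are needed, and SPSS can fit these models. Intervals become wider but valid. The sample was already inflated for clustering, so power remains adequate. At 289 per arm and DE 1.99, the SE is 2.06 × √(2/289) × √1.99 = 0.242, and 0.87/0.242 = 3.60 on 17 df gives about 92%. If DE stays at 2.45 with 22 to 24 analysed per centre, power is about 84 to 86%.

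The procedural cost is a protocol amendment, which the article routes through sponsor permission, ethics approval and the trial registry. It should be made before the analysts are unblinded.

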**Secondary measures**	
-Illness duration	Days from the initial consultation to the day when the patient has reported full recovery based on the patient’s responses to question item A3a in Additional file 1, item B1b in Additional file 2, and item C1b in Additional file 3.
-Illness severity	Ten-point Likert rating of symptom severity based on the patient’s responses to question item A3b in Additional file 1, item B1c in Additional file 2, and item C1c in Additional file 3.
-Times of re-visits	Times of re-visits to the same clinic as the initial consultation + visits to other clinics for the same RTI episode based on the patient’s responses to question items C3a1, C4b12, and C4b22 in Additional file 3.
-Antibiotics re-prescription	Times of antibiotics re-prescription during the patient’s re-visits to the same clinic as the initial consultation and visits to other clinics for the same RTI episode based on the patient’s responses to question items C3a2, C3a3, C3a4, C4a3, C4b15, and C4b25 in Additional file 3.
-Knowledge about and attitude toward antibiotics	Percentage of correct responses to the questions relating to knowledge and attitude about antibiotics, i.e., item D1 in Additional file 4.
-Times of re-occurrence of RTIs	Times of re-occurring RTI episodes 180 days or 365 days following the initial consultation based on the patient’s responses to question item D2a1 in Additional file 4.
-Health service seeking for re-occurred infections	Times of visits to clinics for re-occurring RTI episodes 180 days or 365 days following the initial consultation based on the patient’s responses to question item D2b1-D3c41 in Additional file 4.
-Antibiotics consumption for re-occurred infections	Times of antibiotics prescriptions for re-occurring RTI episodes 180 days or 365 days following the initial consultation based on the patient’s responses to question items D2b3, D2c3, and D3c3 in Additional file 4.
-Quality of life (EQ-5D-5L)	Quality-adjusted life years based on the patient’s responses to the EQ-5D-5L scales in Additional file 5.
-Attitude toward intervention messages	Percentage of ideal responses to the questions relating to attitude toward the intervention messages, i.e., item B3d-B3e in Additional file 2, item C5d-C5e in Additional file 3.
-Understanding of intervention messages	Percentage of ideal responses to the questions relating to the understanding of the intervention messages, i.e., item B3c in Additional file 2, item C5c in Additional file 3.

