#### Data collection

The study data will be collected through one baseline and five follow-up telephone interviews. For any recruited patient, the baseline interview happens immediately after the consultation, while the follow-up interviews are scheduled at 7, 14, 21,180, and 365 days after the baseline. The interviews will be performed by trained data collectors using a structured questionnaire adapted from our previous study [18] (Additional files 1, 2, 3 and 4). The main content of the questionnaire includes patient demographic characteristics (e.g., sex, age, education, residential area, and medical insurance status), illness duration, symptoms, severity rating, diagnosis, antibiotics, and other medicines prescribed. EPI DATA 3.1 will be used to create a data entry interface for all the on-site and telephone follow-up interviews. Table 3 summarizes measure by measure time schedule for data collection.

**Table 3 Tab3:** SPIRIT schedule of outcome measures

**Category**	**Outcome measure**	**Initial consultation**	**Days after consultation**				
			**7**	**14**	**21**	**180**	**365**
Primary measure	Number of days with antibiotics use	√	√	√	√		
Secondary measures	Illness duration	√	√	√	√		
	Illness severity	√	√	√	√		
	Times of re-visits				√		
	Antibiotics re-prescription				√		
	Knowledge about and attitude toward antibiotics					√	√
	Times of re-occurrence of RTIs					√	√
	Health service seeking for re-occurred infections					√	√
	Antibiotics consumption for re-occurred infections					√	√
	Quality of life (EQ-5D-5L)	√	√	√	√		
	Attitude toward intervention messages		√	√			
	Understanding of intervention messages		√	√			

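### QALYs and, by implication, symptom severity are compared by an unadjusted t-test although their baseline values are already collected: adjusting for baseline is a nearly free improvement

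*Protocol article*

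**What the plan says.** The Data analysis section gives one rule for comparing numerical variables between the two groups: a t-test of "independent samples for mean comparisons will be carried out". No section of the article names a covariate, a change score, a regression or a mixed model. The list of between-arm comparisons in the same section includes "quality of life; times of re-occurrence of RTIs and related health service seeking". Illness severity is not on that list. It is a secondary outcome under Outcome measures, though, and the t-test is the only rule offered for a numerical variable.

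Table 2 defines quality of life as "Quality-adjusted life years based on the patient’s responses to the EQ-5D-5L scales in Additional file 5". It defines severity as "Ten-point Likert rating of symptom severity based on the patient’s responses to question item A3b in Additional file 1", together with the corresponding follow-up items. Table 3 ticks EQ-5D-5L and "Illness severity" at the initial consultation and at days 7, 14 and 21. The Data collection section places the baseline interview directly after the consultation. According to the Usual care section, the messages come in the days after that consultation.

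**The concern.** Both outcomes have a value recorded before the first message, and the stated test does not use it. A patient's baseline score normally predicts the later score. An arm difference already present at baseline therefore passes in part into the follow-up difference, and the predictable part of the patient-to-patient variation stays in the error term.

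For QALYs there may be a more direct route. If the QALY is computed from day 0, the baseline utility is part of the outcome itself. With 12 centres per arm, chance baseline differences are larger than the number of patients alone would suggest. What is at stake is how sharply, and in a given realisation how fairly, the trial answers its third objective (quality of life) and its severity outcome.

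**Working it through.** **The plan's own figures.** With a difference of 0.87 days, SD 2.06, two-sided alpha 0.05 and 90% power (Sample size section):

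n = 2 × (1.960 + 1.282)² × 2.06² / 0.87² = 117.8, so 118 per arm.

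2.45 × 118 × 2 × 1.2 × 1.2 = 832.6, so 833 patients, or 833/24 ≈ 35 per centre and 12 × 35 = 420 per arm. Both stated figures reproduce. The article gives no figure for QALYs or severity.

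**Weight of baseline in a QALY.** This assumes an area under the curve by the trapezoid rule over the four Table 3 time points. The day weights are 3.5, 7, 7 and 3.5, which sum to 21. The baseline share is 3.5/21 = 0.167, about 17%. The largest possible 21-day QALY is 21/365 = 0.0575.

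**Chance imbalance in utility.** This assumes a utility SD of 0.10 to 0.20 and borrows the design effect of 2.45, which the Sample size section gives for a calculation based on antibiotic days.

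SE of the baseline arm difference = SD × √(2 × 2.45/420) = 0.108 × SD, which is 0.011 to 0.022.

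As an illustration, take a baseline gap of 0.03 that persists at half size through follow-up:
- Contribution to the QALY difference: (0.03 × 3.5 + 0.015 × 17.5)/365 = 0.0010.
- A true gain of 0.02 utility at every follow-up: 0.02 × 17.5/365 = 0.00096.

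The two are about equal. A gap of 0.03 is 1.4 SE at SD 0.20 (two-sided chance about 17%) and 2.8 SE at SD 0.10 (about 0.5%). The illustration is therefore realistic mainly at the upper SD.

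**Chance imbalance in severity.** With 118 effective patients per arm, the SE of the baseline difference is √(2/118) = 0.13 SD, and its 95% range is about ±0.26 SD. If arm means follow the same correlation as patients, an imbalance at the edge of that range moves the follow-up difference by rho × 0.26 SD: 0.10, 0.13 or 0.15 SD for rho 0.4, 0.5 or 0.6 (from the unrounded 0.255).

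**Precision.** Let rho be the correlation of the outcome with its baseline covariate (assumed 0.4, 0.5 or 0.6). Patient-level residual variance falls by rho²: 16%, 25% or 36%. The variance of the arm difference also has a between-centre part:
- Implied ICC = (2.45 − 1)/(35 − 1) = 0.043.
- Between-centre share = 35 × 0.043/2.45 ≈ 61%, which leaves about 39% at patient level.
- If adjustment leaves the between-centre part unchanged, the arm-difference variance falls by 0.39 × 16%, 25% or 36%, that is about 6%, 10% or 14%.

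The gain would approach 16% to 36% only if baseline explained the same share of the variation between centres. The article gives nothing from which to judge that.

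**The case against.** The strongest reply is that randomisation already protects the comparison. Over repeated allocations an unadjusted difference is unbiased, and a correct standard error covers chance imbalance. This stands. A reader might infer from the missing adjustment that the QALY and severity estimates are invalid; the document does not support that. The loss is in precision and in robustness to the imbalance that actually occurs.

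A reader might also infer that imbalance is likely because unblinded staff enrol patients after allocation. The article does not settle this. The allocation section places randomisation after baseline data collection is complete. Patient recruitment describes investigators sent to centres already in an arm, the blinding section leaves site investigators unblinded, and messages follow directly on each consultation. If enrolment does follow allocation, the fault would be differential recruitment, which a single baseline score cannot remove.

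Three further objections hold in part:
- The QALY formula is not given, and such detail is commonly left to an analysis plan, so the 17% is conditional on an assumed formula.
- The use of the t-test for severity is inferred, since severity is not on the list of comparisons and no endpoint time is named.
- The same sentence also ignores clustering, which is a separate and larger matter. A mixed model without the baseline covariate would repair that and leave this point open.

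The reply that an analysis plan may supply the adjustment carries less weight. The article fixes a method for numerical outcomes, and a covariate-adjusted model would depart from it.

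**Conclusion.** The point holds as a free improvement to a stated method. Baseline EQ-5D-5L and severity are scheduled, and the t-test does not use them. For rho of 0.4 to 0.6, patient-level residual variance would fall by 16% to 36%. The variance of the arm difference may fall by only about 6% to 14%, unless baseline also explains variation between centres.

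These sizes rest on assumed correlations and on a design effect carried over from antibiotic days. The QALY weight also rests on an assumed area under the curve from day 0. Two secondary outcomes are concerned; the primary outcome and the 833 are untouched.

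**What to change.** For QALYs and follow-up severity, replace the t-test with a linear mixed model containing:
- arm;
- county as a fixed effect, since centres are randomised two to two within county;
- health centre as a random effect;
- baseline EQ-5D-5L utility (for QALYs) or baseline severity (for follow-up severity) as covariate.

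Health centre must be random: every patient of a centre is in the same arm, so with fixed centre effects the arm effect could not be estimated.

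The cost is a change of analysis wording. No new data, visits or patients are needed. The change would not cure differential recruitment by unblinded staff, should that occur.
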